## Abstract

**Background:**

The analgesic efficacy of liposomal bupivacaine (LB) for ultrasound-guided erector spinae plane block (ESPB) and thoracoscopic intercostal nerve block (ICNB) in thoracic surgery remains uncertain. This study aims to evaluate the analgesic efficacy of anesthesiologist-performed ESPB using LB versus surgeon-administrated ICNB with LB in patients undergoing video-assisted thoracoscopic surgery (VATS) lung resection.

**Methods:**

This single-center, prospective, randomized, double-blinded trial will include 120 adult patients scheduled for VATS lung resection. Patients will be randomly assigned 1:1 to the ESPB group or ICNB group. Each patient will receive either an ESPB or ICNB at the end of the surgery, along with patients-controlled intravenous analgesia (PCIA) as part of a postoperative multimodal analgesia. The primary outcome is the average numeric rating scale (NRS) pain scores at rest over 72 h postoperatively (average of three 24-h time points: 24, 48, and 72 h). Secondary outcomes include NRS pain scores at rest and during activity at 24, 48, and 72 h postoperatively, Quality of Recovery 15 scores at 24, 48, and 72 h postoperatively, time to first press on the PCIA device, total opioid consumption within 72 h postoperatively, time to initiate independent bedside mobilization, length of postoperative hospital stay, and the incidence of chronic pain (defined as an NRS score ≥ 1) at 3 months post-surgery. Analyses will be performed in the modified intention-to-treat population.

**Discussion:**

We hypothesize that anesthesiologist-performed ultrasound-guided ESPB with liposomal bupivacaine will result in lower average numeric rating scale pain scores over 72 h compared to surgeon-administrated thoracoscopic ICNB in patients undergoing VATS lung resection. The findings of this study aim to provide evidence to optimize postoperative analgesic regimens for patients undergoing VATS lung resection.

**Clinical trial registration:**

http://www.chictr.org.cn, identifier ChiCTR2400092927.

## Introduction

Minimally invasive thoracic surgery such as video-assisted thoracoscopic surgery (VATS) has become the predominant approach for lung resection over the past decade (1). Despite its minimally invasive nature, VATS can still cause significant pain in 25–44% of patients, with some experiencing chronic pain lasting for months or even years, profoundly impacting their quality of life (2–4). Consequently, multimodal analgesia, particularly regional nerve block techniques, has become essential for patients undergoing VATS lung resection. However, the effectiveness of these techniques is often limited by the relatively short duration of standard local anesthetics, which typically last less than 24 h. Liposomal bupivacaine (LB) is a long-acting local anesthetic encapsulating water-soluble bupivacaine within liposomes, providing sustained drug release for 72–96 h (5). Initially approved by the U.S. Food and Drug Administration in 2011 for single-dose wound infiltration to manage postsurgical analgesia in adults, its use has since expanded to include fascial plane blocks, showcasing safety in various clinical settings (6, 7).

LB is frequently employed as postoperative analgesia for intercostal nerve blocks (ICNB) in thoracic surgery, and ICNB can be easily performed by surgeons during VATS (8, 9). Due to the limited specific dermatomal distribution of its analgesic effect, the ability of ICNB to provide superior pain control following thoracoscopic procedures remains controversial (10, 11). The erector spinae plane block (ESPB), first introduced in 2016 (12), has emerged as a promising interfascial plane block technique for thoracic pain management, known for its simplicity, high safety profile, and reliable analgesic effectiveness (13, 14). Recent studies comparing ESPB and ICNB using plain local anesthetics in thoracic surgery have yielded inconsistent results. One study demonstrated that ESPB with plain local anesthetics provides superior analgesia and reduces perioperative analgesic requirements compared to ICNB in patients undergoing mini-thoracotomy (15). Another study reported comparable postoperative analgesic effects between the two groups in patients undergoing VATS lung resection (16). To date, no prospective studies have compared the analgesic efficacy of LB when used in anesthesiologist-performed ultrasound-guided ESPB versus surgeon-administrated thoracoscopic ICNB in thoracic surgery.

Therefore, we designed this randomized controlled trial to evaluate the effects of LB when used in these two techniques on postoperative pain in patients undergoing VATS lung resection. We hypothesized that patients receiving anesthesiologist-performed ultrasound-guided ESPB with LB would have lower average numeric rating scale pain scores over 72 h compared to those receiving surgeon-administered thoracoscopic ICNB.

## Methods

### Ethics and registration

The study protocol was approved by the Clinical Research Ethical Committee of the First Affiliated Hospital of Soochow University (Approval No. 2024–411) on September 30, 2024. The study was registered at the Chinese Clinical Trial Registry^1^ (identifier: ChiCTR2400092927). Written informed consent will be obtained from all participants before inclusion in the study. This protocol adheres to the guidelines outlined in the Standard Protocol Items: Recommendations for Interventional Trials (SPIRIT) statement (17).

### Study design and participants

This is a single-center, prospective, randomized, double-blinded clinical trial. This trial start date is 1 December 2024, with an anticipated completion date of 31 December 2025. The study flow diagram is presented in Figure 1. According to the SPIRIT statement, the patient recruitment, study interventions, and outcome measurement schedule are shown in Table 1.

**Figure 1 fig1:**
[figure not shown]
Study flow diagram. ESPB, erector spinae plane block; ICNB, intercostal nerve block.

**Table 1 tab1:** Schedule of patient enrollment, study interventions, and outcome measurements.

Timepoint	Study period								
	Enrollment	Allocation	Post-allocation						Close-out
	Preoperative visit	specimen removal	End of surgery	PACU	24 h after surgery	48 h after surgery	72 h after surgery	Hospital discharge	90 d after surgery
Enrollment									
Eligibility screening	**╳**								
Written informed consent	**╳**								
Demographic data	**╳**								
Randomization		**╳**							
Allocation		**╳**							
Interventions									
ESPB			**╳**						
ICNB			**╳**						
Measurements									
Pain scores at rest					**╳**	**╳**	**╳**		
Pain scores on activity					**╳**	**╳**	**╳**		
QoR-15 scores					**╳**	**╳**	**╳**		
First press on the PCIA device				**╳**	**╳**	**╳**			
Opioid consumption				**╳**	**╳**	**╳**	**╳**		
Initiate independent bedside mobilization					**╳**	**╳**	**╳**		
Postoperative hospital stay								**╳**	
Adverse events^a^				**╳**	**╳**	**╳**	**╳**		
Incidence of chronic pain									**╳**

According to SPIRIT statement of defining standard protocol items for clinical trials. PACU, post-anesthesia care unit; ESPB, erector spinae plane block; ICNB, intercostal nerve block; QoR-15, Quality of Recovery-15; PCIA, patient-controlled intravenous analgesia.

a Including postoperative nausea and vomiting (PONV), fever, headache, dizziness, itching, constipation, ileus, urinary retention, insomnia, new-onset atrial fibrillation, severe ventricular arrhythmia, cardiac arrest, chest tightness, pulmonary embolism, Pulmonary atelectasis, pneumothorax, chylothorax, Pneumothorax, deep vein thrombosis and organ failure.

Participants in this study should meet the following inclusion criteria: (1) American Society of Anesthesiologists (ASA) class I-III. (2) Aged between 18 and 75 years. (3) Scheduled for elective video-assisted thoracoscopic lung resection under general anesthesia. Participants will be excluded if they have any of the following conditions: (1) sinus bradycardia (heart rate < 50 bpm) or heart block (sinoatrial or atrioventricular block); (2) left ventricular ejection fraction <40%; (3) unstable coronary artery disease; (4) hepatic disease (Child-Pugh classification C) or renal failure (receiving renal replacement therapy); (5) diabetic neuropathy; (6) coagulation dysfunction; (7) infection at the puncture site; (8) history of Parkinson’s or Alzheimer’s disease; (9) history of epilepsy; (10) neurological disorders (e.g., stroke, hypoesthesia); (11) uncontrolled psychiatric disorders (e.g., anxiety, depression, schizophrenia); (12) pregnancy or breast feeding; (13) history of chronic pain or preoperative use of sedative and analgesic drugs; (14) allergy to local anesthetics or any trial-related medication.

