After surgery, all patients are provided with patient-controlled intravenous analgesia (PCIA), consisting of 100 μg sufentanil diluted to 100 mL with normal saline (final concentration: 1 μg/mL). The PCIA device is programmed with the following parameters: a background infusion rate of 1 mL/h, a self-controlled bolus of 2 mL, a lockout interval of 10 min, and a maximum hourly dose of 20 mL. The PCIA is initiated immediately after surgery and continues for 48 h postoperatively. If pain persists, defined as a numeric rating scale (NRS) pain score of ≥4, patients are instructed to self-administer sufentanil via PCIA. If pain remained unrelieved, intravenous rescue opioids (sufentanil, fentanyl, oxycodone, tramadol, or morphine) were permitted. Additionally, both groups will receive an initial intravenous dose of 50 mg flurbiprofen axetil at the end of surgery. This will be followed by two daily doses of 50 mg intravenous flurbiprofen axetil administered at 08:00 and 16:00 (totaling 100 mg per day) as part of the multimodal analgesia regimen on postoperative days 1 and 2.

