### Perioperative management

Upon arrival in the operating room, patients receive standard monitoring, including non-invasive blood pressure measurement, electrocardiography, pulse oximetry (SpO_2_), and temperature monitoring. Following anesthesia induction, all patients undergo left or right radial artery catheterization for continuous arterial blood pressure monitoring. The anesthesia induction procedure follows a standardized protocol, involving the sequential administration of propofol (2–2.5 mg/kg), sufentanil (0.3–0.5 μg/kg), and cisatracurium (0.1–0.2 mg/kg). Endotracheal intubation is performed using a double-lumen tube for lung isolation, with proper positioning verified via fiberoptic bronchoscopy. The intraoperative mechanical ventilation protocol followed established lung-protective strategies (18). During one-lung ventilation, tidal volumes were set at 4–6 mL/kg, with an initial PEEP of 5 cmH₂O, followed by individualized adjustment. The inspired oxygen fraction and respiratory rate were modified to maintain SpO₂ ≥ 95% and end-tidal carbon dioxide (EtCO₂) levels between 35 and 45 mmHg during both one-lung and double-lung ventilation. Lung recruitment maneuvers were performed when clinically indicated. Anesthesia is maintained with sevoflurane inhalation, targeting a bispectral index value between 40 and 60. Intraoperative analgesia is provided with sufentanil and remifentanil: sufentanil 0.1–0.2 μg/kg is administered before surgical incision, and remifentanil (0.05–0.2 μg/kg/min) is continuously infused throughout the procedure. Sufentanil (0.1–0.2 μg/kg) is given when the remifentanil infusion is discontinued at the end of the operation. Incremental doses of cisatracurium are given intraoperatively as required.

Intraoperative hypotension (defined as a mean blood pressure [MBP] decrease of >30% from baseline or an MBP of <65 mmHg) would be treated with intravenous ephedrine of 6–10 mg or phenylephrine of 50–100 μg, and bradycardia (defined as heart rate [HR] of <50 beats/min) would be managed with intravenous atropine of 0.3–0.5 mg or ephedrine bolus if coexisting hypotension is present. Hypertension (defined as an MBP increase of >30% of baseline) will be treated with intravenous urapidil 5–10 mg. Tachycardia (defined as HR > 100 beats/min) will be treated with intravenous esmolol 10–20 mg.

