### Data monitoring committee

An independent Data Monitoring Committee (DMC) has been established to address any uncertainties related to data collection and registration. The DMC is composed of a chair (an experienced anesthesiologist), a professor of statistics, a pharmacologist, and a thoracic surgeon. If any ambiguity arises in data collection or registration, DMC will discuss these issues to reach a final consensus.

Both intervention methods are routinely performed at our center, and we anticipate that serious adverse events during this study will be infrequent. Any adverse event, whether related to the study interventions or not, must be reported to the DMC within 24 h using an “Adverse Event Form.” In the event of serious adverse events, such as unexpected deterioration of patients’ clinical status post-surgery, the research team could request unmasking of allocation and adjust or discontinue the study medications. The DMC will conduct ongoing reviews to assess safety and provide recommendations regarding the suspension or termination of the study.

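### The renal exclusion covers only patients on renal replacement therapy, so a patient with severe renal impairment not on dialysis is eligible and scheduled for five doses of flurbiprofen axetil

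*Protocol article*

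**What the plan says.** The protocol article prints a numbered list of 14 exclusions under Study design and participants. Criterion (4) reads "hepatic disease (Child-Pugh classification C) or renal failure (receiving renal replacement therapy"), so for the kidney the line is dialysis or an equivalent treatment. Criterion (14), the only one that refers to the trial's drugs, is "allergy to local anesthetics or any trial-related medication".

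Under Study interventions, "both groups will receive an initial intravenous dose of 50 mg flurbiprofen axetil at the end of surgery", followed on postoperative days 1 and 2 by "two daily doses of 50 mg intravenous flurbiprofen axetil administered at 08:00 and 16:00". No omission rule, dose reduction or substitute is printed.

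Table 1 places eligibility screening at the preoperative visit. On safety during the trial, the Data monitoring committee section states: "Any adverse event, whether related to the study interventions or not, must be reported to the DMC within 24 h". After a serious adverse event, "the research team could request unmasking of allocation and adjust or discontinue the study medications". Organ failure within 72 h is among the safety outcomes.

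**The concern.** The article does state a renal threshold, but that threshold does not fit a drug that it schedules for everyone. It removes patients already on renal replacement therapy and keeps those with severely reduced renal function who are not on it. The latter still have function to lose, and NSAIDs are generally avoided in them.

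What is at stake is avoidable harm to a small number of eligible patients. A clinician who withholds the drug, as many would, departs from the printed regimen with no stated rule on what to do instead. The comparison of the two blocks is not threatened.

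**Working it through.** No statistical calculation is involved. The check sets the eligibility rules against the scheduled regimen.

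**Dose scheduled per patient** (inputs from Study interventions)
- Daily dose on postoperative days 1 and 2: 2 × 50 mg = 100 mg, which reproduces the article's own daily total.
- Number of doses: 1 + 2 days × 2 = 5.
- Total: 50 mg + 2 × 100 mg = 250 mg.

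**A test patient put through the printed criteria.** Take a 65-year-old in ASA class III, scheduled for elective VATS lung resection, with severe renal impairment, not on dialysis and without drug allergy.
- Inclusion: age 18 to 75, ASA I to III and elective surgery are all met.
- Criterion (4), renal part: not met, because the patient receives no renal replacement therapy. Hepatic part: not met unless the patient is Child-Pugh C.
- Criterion (14): not met, because there is no allergy.
- Other criteria that bear on NSAID risk: coagulation dysfunction, ejection fraction below 40%, unstable coronary disease, pregnancy or breast feeding, and preoperative analgesic use. Each removes some patients at higher risk, but none is triggered by renal impairment alone.

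The patient is eligible and is scheduled for all five doses.

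**Whether anything printed stops the first dose.** Adverse-event reporting, committee review, adjustment of study medication after a serious event and the organ-failure outcome all respond to something that has already happened. None acts before the dose at the end of surgery. The printed step that could is preoperative screening, and it applies the criteria above.

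**What the point does not touch.** The sample size rests on a standard deviation of 1.75, a difference of 1 point, 80% power and 15% dropout. None of these depends on flurbiprofen, which is the same in both arms.

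**The case against.** The strongest reply is that the two sections do not contradict each other on their face. They clash only once one adds that NSAIDs are avoided in severe renal impairment, which the article does not say. That is true, and the premise is stated below as an assumption. It is basic clinical knowledge rather than a figure recalled from a source, and the conclusion needs nothing more precise.

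A second reply is that a journal article condenses the full protocol, which may contain a clause on clinical judgement, and that flurbiprofen is background care. This has force against any complaint about silence. It has less against the renal point, because the article is not silent: it prints a renal cut-off. A fuller document would have to override that cut-off or qualify the dosing sentence.

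Three stronger readings are tempting, and the article does not support them.
- A reader might extend the point to every NSAID contraindication, such as active peptic ulcer or recent gastrointestinal bleeding. The article sets no criterion for these, so their absence may be no more than condensation.
- A reader might infer that the article marks every discretionary drug, so that the lack of such wording makes flurbiprofen strictly compulsory. The examples do not show this. "Incremental doses of cisatracurium are given intraoperatively as required" describes titration, and "intravenous rescue opioids (sufentanil, fentanyl, oxycodone, tramadol, or morphine) were permitted" describes escalation. Neither is a waiver for contraindication. Ondansetron is also given to all patients without one.
- A reader might use the number of doses given before the first scheduled ward check as a measure of risk. Every patient is scheduled for those doses, so the count says nothing about how many are vulnerable. Adverse-event reporting is also not confined to scheduled visits.

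**Conclusion.** The point holds in a narrow form. On the printed text, a patient with severe renal impairment who is not on dialysis is eligible and is scheduled for 250 mg of flurbiprofen axetil over five doses, and no printed safeguard acts before the first.

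This rests on two assumptions: that flurbiprofen axetil, as an NSAID, is generally avoided in such patients, and that the full protocol, which is not shown, does not already provide an exemption. The number of patients affected cannot be derived from the article. It is probably small, and clinicians would probably withhold the drug in obvious cases.

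This is an optional, low-cost safety correction. It is not a claim of bias, of lost power or of a flaw in the analysis.

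**What to change.** Either of two changes is enough.

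1. **Change eligibility.** Reword criterion (14) along these lines: *allergy or contraindication to local anesthetics or any trial-mandated medication, including severe renal impairment not on dialysis (eGFR below a limit set by the sponsor)*. Apply it at the preoperative visit, where screening already takes place. The cost is one phrase, a check of history and laboratory results, and a slightly narrower population.
2. **Change the regimen.** Add *unless contraindicated* to the flurbiprofen sentence and record each omission with its reason. Decide this at the preoperative visit: randomization happens at specimen removal, before the first dose, and an earlier decision cannot be influenced by allocation. The cost is a few patients without the background NSAID. They would stay in the modified intention-to-treat population on the same terms as everyone else.

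The second is less restrictive and keeps the population as planned; the first keeps background analgesia uniform. Neither needs a change to the sample size or the analysis.

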### Randomization and blindness

An independent statistician, who will not participate in the study or data management, will generate a randomization list using an online tool^2^ with an allocation ratio of 1:1 and block sizes of 2 and 4. Randomization will be performed intraoperatively at the time of surgical specimen removal to minimize post-randomization exclusions. The generated random sequences will be securely sealed in sequentially numbered opaque envelopes stored in a locked cabinet. An independent researcher, who is responsible for patient enrollment, will immediately open the envelope following the removal of surgical specimen to obtain the randomization assignment. All patients will receive either an ESPB or ICNB based on randomization at the end of the surgery under anesthesia, ensuring that patients are blinded to their group allocations. Additionally, investigators involved in the postoperative outcomes data collection and follow-up assessments will remain masked to group allocation. Group allocation will remain concealed until the trial is closed to accrual and the final patient has completed the 3-month study period following surgery.

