### Statistical analysis

Descriptive statistics will be used to summarize baseline characteristics and demographic data without conducting between-group comparisons. Continuous data will be reported as median with interquartile ranges (IQR) or means with standard deviations (SD), depending on data distribution. Categorical data will be displayed as counts and percentages. The independent t-test or the Mann–Whitney U test will be used to assess between-group differences in continuous data, while the Chi-squared test or Fisher’s exact test will be applied for categorical data analysis, as appropriate.

For the study outcomes, the treatment effect of study interventions will be evaluated using odds ratios for binary data and differences for continuous data, each reported with 95% confidence intervals. The primary and secondary outcomes will be further analyzed using multivariable linear regression or logistic regression, adjusting for baseline covariates (age, sex, type of surgery, and number of ports). Subgroup analyses for the average pain score will be performed according to age (<60 years old vs. ≥ 60 years old), sex (female vs. male), BMI (< 25 vs. ≥ 25), surgery type (wedge resection vs. segmentectomy vs. lobectomy), and the number of port (single or multiple). Correction for multiple testing is planned for secondary outcomes using the Benjamini-Hochberg method.

The analysis will be performed on the modified intention-to-treat population, comprising all randomized patients who undergo VATS lung resection and for whom primary outcome are available. We do not plan to conduct missing data imputation or interim analysis. A Two-sided *p-*value of <0.05 will be considered statistically significant. Statistical analyses will be performed with R statistical software (version 4.3.0, R Foundation for Statistical Computing) by independent statisticians.

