ICNB has been shown to provide effective pain relief after thoracic surgery and can be easily performed by surgeons during VATS (33). Recently, long-acting local anesthetics, such as LB, have been increasingly used for postoperative analgesia in ICNB during VATS lung resection. However, the efficacy of LB in controlling postoperative pain control following thoracoscopic procedures remains inconclusive. Several retrospective studies have suggested that LB is superior to bupivacaine hydrochloride for intercostal nerve blocks in managing postsurgical pain after thoracic surgery, including reducing postoperative opioid consumption and shortening hospital stays (34, 35). In contrast, two randomized controlled trials found that LB for intercostal nerve block did not offer superior analgesic or opioid-sparing benefits in the surgery (28, 36). Given that the analgesic effect of ICNB is often confined to a specific dermatomal distribution and requires multiple injections at each targeted intercostal space (10, 11), ESPB is easier to perform and provides a broader spread of local anesthetic, extending to paravertebral space, intercostal space, and neural foramina (37). Recent clinical practice increasingly favors ESPB over ICNB for postoperative management in thoracic surgery. A recent randomized controlled trial involving 60 consecutive adult patients undergoing mini-thoracotomy for lung resection indicated that ESPB provided superior analgesia, reduced perioperative analgesic consumption, and caused less respiratory muscle strength impairment compared to ICNB (15). Another randomized controlled study suggested that for minor pulmonary resection, where prolonged postoperative pain is not a concern, thoracoscopic ICNB may be beneficial due to its effectiveness in analgesia and procedural convenience. However, for more complex pulmonary surgeries associated with prolonged postoperative pain, ESPB appears to be a preferred option (16). These findings have predominantly relied on the use of plain local anesthetics. To date, this is the first randomized controlled study to compare the efficacy of anesthesiologist-performed ESPB and surgeon-administrated ICNB with LB in VATS lung resection, incorporating a comprehensive pain intensity assessment at 3 time points from 0 to 72 h postoperatively.

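### The cited rationale suggests the better block may depend on the extent of resection, so the primary model should adjust for surgery type and the treatment-by-surgery-type contrast should lead the subgroup analyses

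*Protocol article*

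**What the plan says.** All quotes are from the protocol article.

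- **Eligibility** (Study design and participants): "Scheduled for elective video-assisted thoracoscopic lung resection under general anesthesia". Extent of resection is not restricted.
- **Allocation** (Randomization and blindness): "with an allocation ratio of 1:1 and block sizes of 2 and 4". No stratification factor is named. On timing: "Randomization will be performed intraoperatively at the time of surgical specimen removal to minimize post-randomization exclusions". The type of resection is therefore essentially known when the envelope is opened.
- **Rationale** (Discussion): one cited randomized trial of the two techniques is reported to distinguish by extent of surgery. On the smaller operations: "for minor pulmonary resection, where prolonged postoperative pain is not a concern, thoracoscopic ICNB may be beneficial". Two reasons are given, analgesic effect and ease of carrying out the block. On the larger operations: "for more complex pulmonary surgeries associated with prolonged postoperative pain, ESPB appears to be a preferred option". The article then adds a caution: "These findings have predominantly relied on the use of plain local anesthetics". The Introduction summarizes the same cited study as showing comparable analgesia overall.
- **Analysis** (Statistical analysis): continuous outcomes are compared by an independent t-test or a Mann-Whitney test. Primary and secondary outcomes are then further analyzed by regression on age, sex, type of surgery and number of ports. The average pain score gets subgroup analyses by age, sex, BMI, "surgery type (wedge resection vs. segmentectomy vs. lobectomy") and number of ports, in no order of priority.
- **Hypothesis** (Introduction and Discussion): lower average pain with ESPB, stated for VATS lung resection as a whole.

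**The concern.** The article gives a reason to think that the difference between the blocks could vary with the extent of resection, and then asks one pooled question of all resections. Two separate things follow.

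1. Surgery type plausibly predicts pain. With no stratification and an unadjusted main test, any chance difference in surgery type between the arms adds noise to the primary estimate.
2. If the effect itself varies by surgery type, the pooled difference is an average weighted by the types that happen to be enrolled. A small or null overall result could then be misread as ESPB giving no benefit in the larger resections, where the cited trial favors it.

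The analysis that speaks to the second question is planned, but it has the same standing as four other subgroup factors for which the article offers no comparable rationale.

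**Working it through.** **Inputs from the article (Sample size calculation, Statistical analysis):** difference 1 NRS point, SD 1.75, power 80%, two-sided alpha 0.05, dropout 15%, 60 per arm. Evaluable: 60 × 0.85 = 51 per arm.

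**Assumptions, not in the article:** the case mix, the size of any prognostic effect of surgery type, the size of any difference in treatment effect, and a two-class split (wedge or minor against the rest).

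**1. The stated sample size reproduces.** A two-sample t-test (noncentral t) needs 50 per arm (power 80.8%; 49 gives 79.96%). 50 / 0.85 = 58.8, so 59 per arm or 118 in total, within two patients of the stated 120.

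**2. How large can chance imbalance be?** With a 40% wedge share and 60 per arm, the SD of the between-arm difference in share is about √(0.4 × 0.6 × 2/60) = 0.089, so the 95% range is ±1.96 × 0.089 = ±0.175, about 18 percentage points. Simulation of unstratified blocks of 2 and 4 with 102 evaluable patients, and a major-resection share of 20% to 50%, gives an SD of 0.08 to 0.10. A difference of at least 10 points occurs in 18% to 29% of trials, and of at least 20 points in 1% to 4%.

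**3. What does imbalance do to the primary result?** Simulation with 102 patients, a 50% major share, a 1-point prognostic effect of major resection and SD 1.75 within class:

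| Analysis | Mean estimate, no true effect | Type I error | Power, true effect 1 |
|---|---|---|---|
| Unadjusted | 0.009 | 4.5% | 77% |
| Adjusted for surgery type | 0.009 | 4.6% | 80% |

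There is no bias and no inflation of type I error. The gain from adjustment is about 3 percentage points of power. As a cross-check in closed form, the unadjusted SD is √(1.75² + 0.5 × 0.5 × 1²) = 1.82. With 51 per arm the noncentral t gives 78% at SD 1.82 and 82% at SD 1.75, a gain of the same size.

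**4. What does imbalance do to the surgery-type contrast?** With 40% wedge there are 20.4 wedge and 30.6 other patients per arm.
- Balanced: SE = 1.75 × √(2/20.4 + 2/30.6) = 0.707, half-width 1.96 × 0.707 = 1.39 points.
- With an 18-point imbalance (about 25 against 15.8 wedge, 26 against 35.2 other): 1.96 × 1.75 × √(1/25 + 1/15.8 + 1/26 + 1/35.2) = 1.41 points.

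Imbalance barely matters here. The interval is wide because the trial is small. Power for a two-class interaction of 1 point is 26% to 30% at a major share of 30% to 50%, and 51% to 58% for 1.5 points. Three classes would split the sample further.

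**5. What does case mix do if the effect differs?** Take an effect of 0 in minor and 1.5 in major resection. Pooled effect = 1.5 × major share; power at 51 per arm and SD 1.75:

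| Major share | Pooled effect | Power |
|---|---|---|
| 20% | 0.30 | 14% |
| 40% | 0.60 | 40% |
| 60% | 0.90 | 73% |
| 80% | 1.20 | 93% |

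Stratification leaves the shares, and so these figures, unchanged. Main-effect adjustment does not help either: at a simulated 50% share the mean estimate is −0.745 both with and without it.

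**The case against.** The strongest case for leaving the plan alone is that it already handles surgery type twice, by covariate adjustment and by a subgroup analysis on the same three procedures. The cited evidence is hedged and rests mostly on plain anesthetic, whereas both arms here receive the liposomal form. The cited preference for ICNB in minor resection rests partly on convenience, so it does not imply that ESPB has no pain benefit there. Pooling resection types is an ordinary choice in a single-center trial of 120. A named interaction term is also something a condensed article may leave to a full protocol or analysis plan that is not shown.

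Most of this stands, and it rules out three stronger readings that a reader might infer.

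- *That unstratified randomization makes the primary result biased or invalid.* It does not (step 3).
- *That power falls to 40%.* That figure needs an assumed case mix and an assumed zero effect in minor resection. The documents give neither, and under the illustration in step 5 the range is about 14% to 93%.
- *That stratified envelopes would repair the dependence on case mix.* They would not (step 5).

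The objection does not remove two points. The adjusted regression is described as a further analysis after an unadjusted test, and a main-effect term cannot show whether the treatment effect differs by surgery type. The subgroup list also gives no precedence to the one factor that the article's own rationale singles out. That the pattern is unconfirmed with liposomal bupivacaine is a reason to name the contrast in advance.

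**Conclusion.** The point holds as a modest weakness in the ordering of the analyses. The randomization is not at fault. An unadjusted primary test gives up about 3 percentage points of power (77% against 80%), assuming a 1-point prognostic effect and a 50% share of major resections. The loss is smaller if surgery type predicts pain less strongly. The pooled result depends on case mix only if the treatment effect truly differs by resection type. The article raises that possibility but does not establish it for liposomal bupivacaine. The contrast that would inform it has a half-width of about 1.4 points under an assumed 40% wedge share, wider than the 1-point clinically important difference, so it can support interpretation but cannot settle the question.

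**What to change.** In the Statistical analysis section:

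1. Make the linear model adjusted for type of surgery, with the covariates already listed (age, sex, number of ports), the primary analysis of average NRS at rest, in place of the unadjusted t-test or Mann-Whitney test.
2. Name the treatment-by-surgery-type difference, with its 95% CI, as the lead subgroup contrast ahead of the other four factors, and label it supportive. Fix the grouping before unblinding. The half-width above treats wedge against segmentectomy and lobectomy combined, a split that the article does not define.
3. Report the case mix by arm, and beside the overall conclusion.

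Stratified envelopes by surgery type are optional. They are feasible because allocation happens at specimen removal, but are worthwhile only if enrolment has not advanced; the article gives a start date of 1 December 2024. They would improve balance slightly and nothing else.

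Cost: a change of text and one prespecified contrast, with no extra patients. The drawback is a wide interval for that contrast, which must not be read as evidence of no difference.
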